### Statistical approach

A computer based randomization protocol will be generated and applied centrally at the end of the run-in period. Baseline comparability between the two treatment groups will be evaluated with respect to entry criteria. Chi-square and t-tests will be used to assess differences between the two groups on the baseline variables. Any variables that are found to be discrepant between the two groups and that are related to the outcome variables will be treated as co-variates in later analyses.

In order to evaluate the patients' change in D/P_Cr _ratios, two strategies will be employed:

1. Repeated measure ANOVA will be performed on those patients who complete the 10-month observation period on the study medications.

2. The Kaplan-Meier method will be used to estimate the time in which patients are likely to display a ≥ 7.5 % increase in the D/P_Crea _ratio during the 10-month period. All patients started on study medication will be available for this analytical approach.

The same strategies will be used to analyze secondary outcome variables.

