### Primary outcome measure

The primary outcome measure will be the longitudinal change in 4h-D/P_creatinine _in the sequential PET examinations. Differential changes in this parameter will indicate differences in the development of the peritoneal solute transport status over time.

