### Sample size estimation

The primary study outcome is the change in 4h-D/P_Cr _from the time of randomization to the conclusion of the 10-month study period. In a previous trial we demonstrated a 6% increase of D/P_Cr _in children on lactate-buffered PD fluid in contrast to a 4% decrease in D/P_Cr _using bicarbonate buffered fluid within 3 months of exposure, resulting in a statistically significant 10% difference in the evolution of peritoneal creatinine transport rate [13]. Assuming that this effect was at least in part due to the different buffer substances applied, a difference in D/P_Cr _at least 7 ± 10% can be expected when Balance and Bicavera^® ^are applied for 10 months. To detect this difference with a sensitivity of 80% and an error probability of 5%, at least 15 patients per randomization group will be required. Assuming a 50% drop-out rate due to renal transplantation and other reasons in the course of the study, 60 patients will have to be enrolled.

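### Two unranked analyses in different populations serve the one primary outcome, and neither is named as the month-10 change on which the trial was sized

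*Protocol article*

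**What the plan says.** All places are in the Protocol article.

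- **Sample size estimation**: "The primary study outcome is the change in 4h-D/P" creatinine, measured "from the time of randomization to the conclusion of the 10-month study period". One difference (7 ± 10%) is to be detected with 80% power at one 5% error probability, and "at least 15 patients per randomization group will be required". With 50% drop-out this becomes 60 enrolled.
- **Primary outcome measure**: "The primary outcome measure will be the longitudinal change in 4h-D/P" creatinine across the sequential PETs. Study design places these at randomisation and at months 3, 6 and 10.
- **Statistical approach**: for change in D/P creatinine, "two strategies will be employed". The first is a repeated-measures ANOVA, restricted to patients who finish the 10 months on their assigned fluid. The second is a Kaplan-Meier estimate of the time to a rise of 7.5% or more, open to every patient who began a study fluid. The same pair is carried over to the secondary outcomes.

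The article does not say which of the two decides, whether the error probability is shared between them, or what follows if they differ.

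**The concern.** The sizing section sets up one question, one contrast and one error probability. The analysis section answers with two methods that differ in population, in the quantity compared and in their handling of early leavers. Neither is described as the change to month 10.

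Two things are at stake. First, if either result may be presented as the primary finding, the 5% in the sizing section no longer bounds the chance of a false claim. Second, the two can disagree for structural reasons. The time-to-event endpoint counts only rises of at least 7.5%, whereas the previous trial cited for sizing saw a 6% rise with lactate-buffered fluid and a 4% fall with bicarbonate. That mean rise lies below the threshold, and a fall registers only as no event. A real difference in means could therefore appear in one analysis and not in the other, leaving the choice of headline until after the data are seen.

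**Working it through.** **1. The plan's own figure.** Inputs from Sample size estimation: difference 7, SD 10, power 80%, error 5% (sidedness not stated; two-sided taken first).

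n per arm = 2 × (1.960 + 0.842)² × 10² / 7² = 32.04, so 33. One-sided: 2 × (1.645 + 0.842)² × 100 / 49 = 25.2, so 26.

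The stated 15 is not reproduced on the usual reading. If 10% is the SD of the between-arm difference (per-arm SD 10/√2 = 7.07), the result is 17 two-sided or 13 one-sided, which is close to 15. The enrolment step reproduces: 2 × 15 / 0.5 = 60. On every reading the calculation is for **one** comparison at **one** 5% level. Whether 15 is enough is a separate matter.

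**2. Populations.** With 60 enrolled and 50% drop-out, the ANOVA uses about 30 patients and the Kaplan-Meier analysis up to 60.

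**3. False-positive chance if either result counts.** Benchmark for two independent 5% tests: 1 − 0.95² = 9.75%.

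The real tests share patients, so this was simulated: 30 per arm, PETs at 0, 3, 6 and 10 months, SD of the month-10 change 10, no true effect. The tests were a group-by-time ANOVA (Greenhouse-Geisser) in completers and a log-rank test on a rise of at least 7.5 in all patients.

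- 50% drop-out, exchangeable errors: ANOVA 4.6%, log-rank 5.0%, at least one 8.9%.
- 50% drop-out, random slopes: 5.1%, 4.8%, at least one 8.8%.
- No drop-out or 30% drop-out, both covariances: at least one 8.5–9.1%.
- A repeat simulation gave 9.2%.

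The assumed covariance and drop-out pattern (exponential, unrelated to outcome) therefore matter little.

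**4. How often the two would disagree.** With a true difference of 7, gradual, exchangeable errors, 50% drop-out: ANOVA significant 32.0%, log-rank 23.0%, at least one 42.4%. Both: 32.0 + 23.0 − 42.4 = 12.6%. Exactly one: 42.4 − 12.6 = 29.8%. The same arithmetic for the other three scenarios in step 5 gives 29–33%. Some discordance is inevitable with two tests of modest power. The figures show only that a deciding rule would be needed often.

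**5. Does the ANOVA lose power against the month-10 contrast?** Assume the tested term is the group-by-time interaction over four PETs (3 degrees of freedom), with about 15 completers per arm, difference 7, SD 10.

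Noncentral F with exchangeable errors, error variance 10²/2 = 50: λ = (15/2) × Σ(pⱼ − p̄)² / 50.

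- Gradual profile (0, 2.1, 4.2, 7): sum of squares 26.83, λ = 4.02, power 35%.
- Early step (0, 7, 7, 7): sum of squares 36.75, λ = 5.51, power 46%.
- Month-10 t-test: 7 / (10 × √(2/15)) = 1.917, power 46% (48% by the normal approximation).

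Simulated:

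| Effect profile, covariance | ANOVA interaction | Month-10 t-test |
|---|---|---|
| Gradual, exchangeable errors | 32% | 46% |
| Gradual, random slopes | 43% | 44% |
| Early step, exchangeable errors | 42% | 44% |
| Early step, random slopes | 60% | 45% |

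There is a clear loss in one row, almost none in two, and a gain in one.

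**The case against.** The strongest reply has four parts.

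*The 9% is not in the protocol.* Kaplan-Meier is described there as a way of estimating a time. No log-rank test, no significance level for the curves and no either-one-wins rule is stated. The order of listing and the wider population also allow the reading that it complements the ANOVA by bringing in the drop-outs. This stands. A reader might infer that the trial's error rate is 9%; the text supports only that nothing in it prevents this.

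*The power loss is not general.* A reader might infer that the ANOVA is weaker than the sized contrast. The article does not name the tested term, and a planned month-10 contrast within the ANOVA would fit its wording equally well. The sizing section also cites an effect seen within 3 months, which is closer to the early-step rows, where the loss is negligible or reversed. This stands in full.

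*The two outcome descriptions do not conflict.* They concern the same variable over the same period. This largely stands: the Primary outcome measure section is loose, not contradictory.

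*Ranking belongs in a statistical analysis plan.* One that is not shown here could indeed rank the analyses. But the article is not merely silent. It affirmatively sets two analyses side by side for the primary outcome, and neither is stated as the sized contrast. That part of the concern survives.

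**Conclusion.** The concern holds in a limited form. Two co-equal analyses, in populations of about 30 and up to 60 patients, are fixed for one primary outcome that was sized as a single month-10 comparison at 5%. If both are tested at 5% and either may count, the chance of a false claim is about 9%. That figure rests on those two conditions, on a log-rank comparison and on the simulation assumptions above, to which it is not sensitive. It is an exposure the plan leaves open, not a rate the plan declares.

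No general power loss is established. An omnibus group-by-time test, if that is what is meant, would have about 32–35% power against 46% for a gradual effect with exchangeable errors, but loses nothing or gains under other plausible profiles. The low absolute power in that comparison comes from 15 per group with SD 10, not from the choice of analysis. The point should be corrected before analysis. It does not undermine the design.

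**What to change.** In Statistical approach, name one primary test: the between-arm difference in change in D/P creatinine from randomisation to month 10, estimated as a single contrast from a repeated-measures mixed model using all available PETs of all randomised patients, two-sided 5%. Reword Primary outcome measure to match. Label the completer ANOVA and the time to a rise of at least 7.5% as supportive.

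This holds the error at 5% and ties the deciding test to the quantity that was sized. It does not settle whether 15 evaluable patients per group are enough.

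The cost is more than wording. The sponsor can no longer claim success on the time-to-event analysis alone. The primary population moves from completers to all randomised patients, and with 50% expected drop-out the model relies on a missing-at-random assumption for those who leave peritoneal dialysis, for example at transplantation, and have no month-10 PET. The completer analysis can probe that assumption as a sensitivity analysis, although it cannot prove it.

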### Exit criteria

Reasons for permanently discontinuing the study medication are 1) renal transplantation, 2) switch to hemodialysis due to PD technique failure, 3) patient/parent withdrawal of consent of participate, 4) patient moving out of the area to a location with no participating center within reasonable distance, and 5) a severe adverse event.

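### The only analysis of the continuous primary outcome is limited to 10-month completers on study fluid, with 50% loss planned and no primary strategy named; this can bias the comparison and leaves early PETs out of it

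*Protocol article*

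**What the plan says.** The sample size section defines the primary outcome as the "change in 4h-D/P_Cr _from the time of randomization to the conclusion of the 10-month study period", a continuous quantity. It then allows for heavy loss: "Assuming a 50% drop-out rate due to renal transplantation and other reasons in the course of the study, 60 patients will have to be enrolled".

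The Statistical approach section opens its plan for this outcome with "In order to evaluate the patients' change in D/P_Cr _ratios, two strategies will be employed". The two strategies are:

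- **Strategy 1:** "Repeated measure ANOVA will be performed on those patients who complete the 10-month observation period on the study medications".
- **Strategy 2:** "The Kaplan-Meier method will be used to estimate the time in which patients are likely to display a ≥ 7.5 % increase" in D/P creatinine, with the added statement "All patients started on study medication will be available for this analytical approach".

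Neither is called primary, and both are carried over to the secondary outcomes. The Exit criteria list renal transplantation, "switch to hemodialysis due to PD technique failure", withdrawal of consent, moving away and a severe adverse event. The Study design section schedules PETs at randomisation and at months 3, 6 and 10.

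**The concern.** Completing 10 months on the assigned fluid is something that happens after randomisation. If the chance of completing depends on both the fluid and the course of peritoneal transport, the completers in the two arms are no longer comparable groups.

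The protocol's own reasoning makes such a link plausible. Its hypothesis is that the fluids differ in how well they preserve transport. Its Background says that ultrafiltration loss from peritoneal degeneration is becoming the leading cause of non-elective termination of PD. Technique failure ends study treatment.

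Two things are at stake. First, the estimate on which the trial is sized may be distorted. Second, the month-3 and month-6 PETs of children who leave before month 10 do not enter that estimate.

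**Working it through.** **Inputs.** From the sample size section: difference 7, SD 10 (read as the per-arm SD of change), power 80%, error 5% (taken as two-sided), 15 per group, 50% loss, 60 enrolled. From Study design: PETs at months 0, 3, 6 and 10. Equal allocation is assumed.

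**The plan's own figures.** The loss step reproduces: 2 × 15 = 30 evaluable, and 30 / (1 − 0.5) = 60. The 15 does not follow from these inputs: n per arm = 2 × 10² × (1.960 + 0.842)² / 7² = 32.04, rounded up to 33. That is a separate matter. Here 15 is used only as the expected number of completers per arm.

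**Which strategy matches the outcome.** The sizing rests on a mean difference in change at month 10 among the 30 who remain. Strategy 1 analyses change on that scale, in those patients. Strategy 2 analyses time to a rise of at least 7.5%, seen at no more than three post-baseline PETs, and gives no estimate of the month-10 difference.

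**How large could the bias be?** The documents give no share of membrane-related exits, so only a range can be shown.

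*Strong selection.* Assume true mean changes of 7 and 0, SD 10, and 50% leaving. A fraction f of the exits are the children with the largest rise (one threshold for both arms), and the rest leave at random.

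| f | Completer difference |
|---|---|
| 0 | 7.0 |
| 10% | 5.8 |
| 20% | 5.1 |
| 30% | 4.6 |
| 50% | 3.8 |

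*Weaker selection.* Let a fraction q of all patients leave because of a latent risk that correlates r with D/P change.

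| q | r = 0.3 | r = 0.7 | r = 1 |
|---|---|---|---|
| 3% | 6.9 | 6.6 | 6.2 |
| 6% | 6.9 | 6.3 | 5.6 |
| 12% | 6.8 | 5.9 | 4.9 |

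The Background offers one loose anchor for q: almost half of patients switch to hemodialysis within 4 to 5 years. At a constant rate (an assumption), 10 months gives 1 − 0.5^(10/60) = 11% to 1 − 0.5^(10/48) = 13%, or about 7 to 8 of 60. This covers every cause, infection included, so the membrane-related part is smaller.

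**What the unused PETs are worth.** Power = Φ(7 / (10 × √(2/n)) − 1.96).

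- 15 completers per arm: Φ(1.917 − 1.96) = 48% (46% with the t distribution).
- All 30 per arm observed at month 10: Φ(2.711 − 1.96) = 77% (76% with t).
- Mixed model on all PETs, assuming ignorable loss of 5 per arm before each of months 3, 6 and 10, SD 10 at each visit and equal correlation between visits:

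| Correlation | Effective n per arm | Power |
|---|---|---|
| 0.3 | 15.8 | 50% |
| 0.5 | 17.1 | 53% |
| 0.7 | 19.2 | 58% |

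Compared with the 48% from the same normal formula, the gain is about 2 to 10 points. It is small because half of the month-10 values are still missing.

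**The case against.** The strongest reply is that the plan already has an analysis that is not limited to completers. The Kaplan-Meier strategy takes in everyone started on study fluid, so their early PETs can be used there. A reader might infer that the plan as a whole discards half the trial. It does not; that is true of the ANOVA only. This part of the reply stands. Yet Kaplan-Meier is only a partial remedy. It dichotomises at 7.5% and does not estimate the quantity used for sizing. The text does not say how exits are handled; if technique-failure exits are censored, the censoring would be informative.

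A reader might also take the ANOVA to be the main analysis. That is a fair inference from the outcome definition and the completer-based sizing, but the document ranks neither strategy.

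Nor does the plan say that it expects membrane failure to drive the loss. Its wording is "Assuming a 50% drop-out rate due to renal transplantation and other reasons in the course of the study", and the Background sentence describes PD termination in general. If exits are mostly transplants unrelated to transport, the bias is negligible. The larger biases above need strong assumptions about who leaves.

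The count of 30 is an upper figure. The Abstract describes the 60 as a cohort treated during run-in, so anyone lost before randomisation is not an excluded randomised patient.

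Finally, continuing PETs after study fluid is stopped would add little. It is not possible after transplantation or a switch to hemodialysis, and hardly practical after withdrawal of consent or a move.

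**Conclusion.** The point holds in a limited form. No primary strategy is named, and the only analysis of the continuous primary outcome is conditioned on completing 10 months on study fluid. That choice is stated in the document itself, so it is not a detail left to an analysis plan. It affects up to about 30 of 60 patients.

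The accurate statement is that the analysis *can* bias the comparison, not that it does. Under the assumptions shown, a true difference of 7 would appear as anything from 7.0 (exits unrelated to transport) through 6.3–6.9 (3–6% of patients leaving, correlation 0.3–0.7) to 4.6 (30% of exits being the largest rises), and lower still if more exits are of that kind. Where such selection acts, it pulls towards no difference. The documents do not allow a choice among these values.

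Using all PETs would raise power only modestly, from about 46–48% to about 50–58%. Those figures rest on a per-arm SD of 10, a two-sided 5% test, 15 completers per arm and the assumed pattern of loss.

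**What to change.** Name one primary analysis: a likelihood-based mixed model for repeated measures on D/P creatinine in all randomised patients, analysed in the arm assigned. It should use every available PET, with the between-arm difference in change at month 10 as the estimate.

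The model assumes that missingness is ignorable given the PETs already observed, which may fail for children who leave through technique failure. Add a sensitivity analysis that departs from this assumption for those exits. Keep the completer ANOVA and the Kaplan-Meier analysis as supportive, and say how exits are treated in the latter. Apply the same ordering to the secondary outcomes that now inherit both strategies.

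The cost is a change of wording and a little more analysis work. No extra patients or visits are needed.

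### The only analysis of D/P creatinine open to all treated children reduces it to time to a ≥7.5% rise, which gives up power against a continuous repeated-measures model of the same data

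*Protocol article*

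**What the plan says.** All references are to the Protocol article.

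- Primary outcome measure: "The primary outcome measure will be the longitudinal change in 4h-D/P" creatinine over the sequential peritoneal equilibration tests (PETs). Sample size estimation describes the same outcome as the change "from the time of randomization to the conclusion of the 10-month study period".
- Sample size estimation works with a mean difference and a spread, "at least 7 ± 10% can be expected when Balance and Bicavera" are given for 10 months. It concludes that "at least 15 patients per randomization group will be required" and doubles the total to 60 for 50% drop-out. It cites an earlier trial with a 6% rise "in children on lactate-buffered PD fluid in contrast to a 4% decrease in D/P" creatinine on bicarbonate fluid.
- Study design places PETs at randomization and at months 3, 6 and 10.
- Statistical approach lists two strategies. The first is repeated-measures ANOVA, restricted to children who finish the 10 months on study fluid. The second reads "The Kaplan-Meier method will be used to estimate the time in which patients are likely to display a ≥ 7.5 % increase in the D/P" creatinine ratio, and of it the section says "All patients started on study medication will be available for this analytical approach".

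**The concern.** The outcome is continuous and the trial is sized on a mean difference, but neither strategy keeps both the measured scale and all the children. With half the children expected to leave, strategy 1 sets aside the PETs of those who leave. Strategy 2 keeps these children but replaces each measured change with whether and when it reached +7.5%. A child who falls by 4% and a child who rises by 7% are scored alike, as not having had the event.

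At stake is how well the broadest comparison can see the effect the trial was designed to find. If strategy 2 is read as the all-patient test, a true 7% buffer effect would more often be reported as no difference than if the same PETs had been analysed as measured.

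**Working it through.** **Inputs from the article.** Difference 7; SD of change 10 (the ±10% read as an SD); 80% power; 5% error (two-sided assumed); 60 children, taken as 30 per arm; 50% drop-out; PETs at months 3, 6 and 10.

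**Assumed, not in the article.** Arm means 7 apart (+4.2/−2.8, +6/−1 or +3.5/−3.5); correlation between visits 0.3 to 0.7; drop-out uniform over 10 months and unrelated to outcome; effect either building linearly to month 10 or fully present from month 3.

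**The plan's own figure.** The drop-out step reproduces: 30/(1 − 0.5) = 60. The 15 per group does not: n = 2 × (1.96 + 0.84)² × 10²/7² ≈ 32, rounded up to 33 per arm (26 one-sided). That is a separate matter, but it means power is limited under any analysis.

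**What completer-only analysis leaves out.** Uniform drop-out of 50% leaves 1 − 0.5 × 3/10 = 85% of children at month 3, 70% at month 6 and 50% at month 10. Per arm of 30 that is 25.5 + 21 + 15 = 61.5 expected follow-up PETs. Completers supply 15 × 3 = 45, so about 16.5 per arm go unused on the measured scale.

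**Effect of the cut at a single visit.** P(change ≥ 7.5) = 1 − Φ((7.5 − mean)/10).

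- Means +4.2/−2.8: 1 − Φ(0.33) = 37.1% against 1 − Φ(1.03) = 15.2%.
- Means +6/−1: 44.0% against 19.8%.
- With 30 per arm and no drop-out, the continuous comparison has power Φ(7/(10√(2/30)) − 1.96) = Φ(0.75) = 77.4%. Comparing the event proportions gives 48.9% and 52.3% for these two pairs.

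**Effect over three visits with 50% drop-out (simulation).** The event is the first observed change of at least 7.5%, censored at the last PET and compared by log-rank. The comparator is a continuous generalised-least-squares model of the same PETs with visit-specific treatment effects. It was given the true covariance and a t reference on month-10 completers minus 2 degrees of freedom. SD is 10 at every visit.

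| Scenario | Log-rank | Continuous, mean of months 3, 6, 10 | Continuous, month 10 |
|---|---|---|---|
| Linear build-up, correlation 0.5, +4.2/−2.8 | 21% | 40% | 47% |
| Full from month 3, same settings | 60% | 81% | 51% |
| Linear build-up, range over all runs | 18–25% | 36–51% | |
| Full from month 3, range over all runs | 50–64% | 69–87% | |

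In the two example rows the visit-averaged test gains 40 − 21 = 19 and 81 − 60 = 21 points. Over all constant-SD scenarios the gain is roughly 15 to 27 points.

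**Sensitivity to the SD.** If the SD grows with the square root of time to 10 at month 10, correlation 0.5 gives log-rank 76–87% against 92–94% for an early effect (loss 7 to 18 points), and a loss of 22 to 27 points under linear build-up. Over all runs with a growing SD the loss is about 7 to 28 points.

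**The case against.** Several points on the other side stand.

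- A reader might infer that the plan expects a fall on bicarbonate. It does not say so. The 4% decrease is a past result, and the Background section shows it came from a three-month crossover against conventional acidic lactate fluid. For this trial only a between-arm difference is projected. The stated hypothesis is better preservation of transport, and a rise as the failure event suits that.
- A reader might infer that the Kaplan-Meier analysis is blind to a fall. It does not grade an individual fall, but a lower arm mean still lowers the event rate: 12.5% at a mean of −4 against 44.0% at +6. The simulations already count this.
- No log-rank or other test is named, and neither strategy is ranked as confirmatory. The section speaks of estimating a time, so the power figures concern a test that is inferred.
- The absence of a reason for 7.5% is weak ground, because a condensed article may leave it to the full protocol.
- Part of the gain comes from the contrast. Sample size estimation defines change to month 10. On that contrast the continuous model gains clearly under linear build-up but not when the effect is early (51% against 60% in the example). With an early effect, log-rank (50–63%) also beats a month-10 completer t-test (44–47%).
- Under linear build-up the recommended test itself reaches only 36–51%, so sample size is the larger limit.

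What these points do not remove is the structure: the measured scale is reserved for completers, and everyone else enters only through a threshold.

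**Conclusion.** The point holds as one of efficiency and choice of scale. The plan has no analysis that uses both the measured D/P creatinine and all treated children, and the threshold analysis discards information already collected. In every scenario tried, a log-rank comparison had less power than the visit-averaged continuous model of the same children and PETs: roughly 15 to 27 points with constant SD, about 7 to 28 if the SD grows with time.

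No single figure for the loss should be read as following from the article. The range depends on the assumed arm means, correlation and time course, on drop-out unrelated to outcome, and on a comparator with known covariance. The advantage over both time courses belongs to the visit-averaged difference, which the Primary outcome measure section's wording of longitudinal change permits; it does not extend reliably to month 10 alone. Nothing here shows the Kaplan-Meier analysis to be invalid.

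**What to change.** In Statistical approach, make the all-patient analysis a likelihood-based repeated-measures model of 4-hour D/P creatinine on its measured scale. Include every randomised child with a baseline and at least one follow-up PET, with terms for treatment, visit, treatment-by-visit and baseline D/P. Pre-specify the treatment difference averaged over months 3, 6 and 10 as the test of longitudinal change. Report the month-10 difference beside it, to match the definition in Sample size estimation. Keep the ≥7.5% Kaplan-Meier curve as a descriptive display.

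The cost is wording: no added children, visits or procedures. The small downside is that the time-to-rise comparison loses any confirmatory role. Children who leave before their first follow-up PET (15% under uniform drop-out) still contribute no follow-up measurement, and the shortfall in sample size needs its own correction.
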